## Abstract

**Background:**

Informal caregivers provide a large part of the care required by people living with dementia. With disease progression, the burden on caregivers typically increases. Dyadic interventions, addressing both the caregiver and the person living with dementia simultaneously, can help to stabilize home care settings. This study examines the effectiveness and cost-effectiveness of an app-assisted dementia care intervention.

**Methods:**

*Living@home* is a two-arm, randomized, controlled, multi-center interventional study designed to evaluate the effectiveness of a dyadic, app-based intervention on home care stability as well as the cost-effectiveness of this approach. The inclusion criteria are a formal diagnosis of dementia and living in their own home for the person with dementia, as well as access to a smartphone and internet for the informal caregiver. A total of 554 dyads will be recruited in five participating memory clinics and randomized (1:1 ratio, using block randomization) into either the intervention or the control group. The intervention group will receive personalized dementia care management for a period of 12 months. A mobile health app connecting caregivers with a Family Care Specialist offers informal caregivers access to memory clinics and Care Specialists at any time, monitoring of their health situation through real-time data collection, overview of care-related tasks, information and alerts tailored to the reported individual caregiver burden. The control group receives care-as-usual. Both groups will be assessed at baseline and after 12 months. The primary outcome is the caregiver’s perseverance time (Perseverance Time Scale), and crucial secondary supportive outcomes are neuropsychiatric symptoms in the person living with dementia (Neuropsychiatric Inventory), and the caregiver’s perceived burden (Zarit Burden Interview). Further secondary outcomes include the caregiver’s resilience and self-efficacy, the dyads’ physiological stress level (as measured by hair cortisol concentrations), health-related quality of life, caregiver depression and anxiety, dyads’ unmet needs, and cost-effectiveness. Intervention effects will be estimated by using multivariate regression analyses.

**Discussion:**

Evidence on the effectiveness and cost-effectiveness of the intervention created from this study can help to inform decision makers and support the transition of the intervention to standard care.

**Trial registration:**

ClinicalTrials.gov NCT07251088, Registered 25.11.2025

## Introduction

### Background and rationale {6a}

In Germany, approximately 84% of the five million individuals in need of care are supported at home by informal caregivers, typically family members. Among these, only 21% receive professional assistance from care or support services, underscoring the substantial burden on informal caregivers [1]. People living with dementia (PlwD) represent a large share of these care recipients, with an estimated 1.8 million individuals affected. On average, they require 36 h per week of informal care—significantly more than individuals with severe diagnoses, such as cancer (16 h/week) or stroke (24 h/week) [2, 3].

Most PlwD and their caregivers (hence referred to as dyads) express a strong desire to remain in their home environment and continue home-based care for as long as possible [4]. Due to the progressive nature of dementia—including increasing cognitive and physical impairments as well as neuropsychiatric symptoms—informal caregivers are continuously challenged to respond to changes in the care situation and to adapt home-based care arrangements to meet evolving needs [5]. Although many caregivers find meaning in their role, the intensive support and care of people living with dementia often lead to both physical and psychological strain on caregivers. This is often associated with depression, anxiety, lower subjective well-being, reduced self-efficacy, and limited social participation [3, 6–9]. Consequently, the sustainability of home care is frequently unstable [10]. Therefore, forty percent of caregivers of community-dwelling PlwD report that they are unable to maintain home care for more than 1 year [11], often resulting in institutionalizations.

Although support services for caregivers have been continuously expanded in recent years, utilization rates remain low [12], often due to a lack of awareness or organizational barriers [13]. Moreover, caregiver workload itself hampers the use of such services. Without adequate support, informal caregiving is increasingly replaced by professional long-term care, placing additional pressure on the scarce personnel and financial resources of the healthcare system [12] and frequently eliciting feelings of guilt in caregivers [13].

To date, randomized controlled intervention trials have only partially demonstrated significant effects on caregiver burden [6]. A meta-analysis revealed that individualized and structured multicomponent interventions, addressing various domains simultaneously, were most effective in reducing caregiver burden [14]. Evidence for the cost-effectiveness of such interventions exists but is limited due to small sample sizes [15]. A model-based analysis suggests that dyadic interventions targeting both PlwD and caregivers may prolong the ability to sustain home care and could potentially be cost-effective [16]. However, findings are mixed, as a meta-analysis of randomized controlled trials on dyadic interventions reported 13 studies with positive outcomes and no effect in 9 others [17]. One reason for the observed inconsistencies may be that the effectiveness of interventions appears to depend on their duration and intensity. Possibly, caregiver needs at times of increasing burden were not always adequately or promptly enough addressed [17]. Digitally supported approaches, such as remote, app-based interventions, could help overcome some of these limitations by providing flexible, immediate support whenever it is most urgently needed. However, research on such digital interventions remains sparse, and it remains unclear to what extent these tools can truly stabilize home care situations.

### Objectives {7}

The primary objectives of the *living@home* study are (1) to assess whether a dyadic care management approach carried out by specialized nurses (Family Care Specialists) combined with the use of a mobile health app providing direct access to a support system (Care Specialists and memory clinics) can stabilize the home care situation, (2) to reduce caregiver burden, and (3) to alleviate neuropsychiatric symptoms in PlwD compared to care as usual.

### Trial design {8}

The *living@home* study is a multi-center, randomized, controlled intervention study with two parallel arms: an intervention arm and a control arm (care as usual). Dyads in the intervention group will receive an individualized dementia care management for a period of 12 months, aiming to identify and effectively address the unmet needs of PlwD and their caregivers. The intervention will be supported by a mobile health app used by both caregivers and Care Specialists, enabling caregivers to access care managers and memory clinics at any time when needs or burdens are faced. Therefore, the app will be used to monitor the caregiver’s health situation and burden through regular real-time data collection, aggregation, and transmission to the care manager for timely interventions or re-interventions tailored to the individual caregiver’s burden. The core items and their respective cut-offs are summarized in Table 1.

**Table 1 Tab1:** App-based monitoring and stratifaction

Item	Source/reference	Cut-off/threshold	Contact with family caregiver	Reassessment frequency
High caregiver distress	PTS and ZBI-12 and ZBI-1	PTS < 6 months or ZBI-12 ≥ 20 or ZBI-1 “extremelx”	Weekly intervention contact	Monthly
Moderate caregiver distress		PTS < 6 and > 24 months or ZBI-12 < 20 or ZBI-1 “quite a bit”	Monthly intervention contact	Monthly
Low caregiver distress		PTS < 24 months or ZBI-12 < 10 or ZBI-1 “not at all/little/moderately”	Quarterly intervention contact	Quarterly

Thus, the intervention frequency and intensity are individualized to the dyads’ needs and the reported burden. Dyads in the control group will receive care as usual. Both groups will be assessed at baseline and after 12 months. The study flowchart is illustrated in Fig. 1.

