The content, the frequency and intensity of the intervention tasks are adjusted according to the caregiver’s burden and the stability of the home care situation, meaning that the higher the burden or the lower the home care stability, the more frequent and intense the intervention will be. Dyads with a low caregiver burden (ZBI-12 < 10 or ZBI-1 “not at all/little/moderately”) and a stable home care arrangement (Perseverance Time Scale > 24 months) are considered as low strain and will be contacted by the Family Care Specialist on a quarterly basis to check on their needs. Dyads with a moderate to high caregiver burden (ZBI-12 10–19 or ZBI-1 “quite a bit”, and ZBI-12 ≥ 20 or ZBI-1 “extremely”) or a moderate to low care arrangement stability (Perseverance Time Scale < 24 months and > 6 months, and < 6 months) are considered as medium to high strain resulting in a monthly or weekly contact frequency, respectively.

Besides these regular contacts (executed via a visit at the home of the PlwD or the caregiver or a phone call or a video call via the mobile health app) the caregivers can reach out to the Family Care Specialists anytime to seek assistance or advice. 

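### Table 1 contradicts itself and the intervention description on the PTS and ZBI-12 thresholds that set intervention intensity

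*Protocol article*

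**What the plan says.** The rule is printed twice in the protocol article.

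**Trial design, Table 1.** Each row lists alternative criteria.
- High distress: "PTS < 6 months or ZBI-12 ≥ 20 or ZBI-1" at its top answer. Contact is weekly and reassessment monthly.
- Moderate distress: "PTS < 6 and > 24 months or ZBI-12 < 20", or ZBI-1 at its second-highest answer. Contact and reassessment are monthly.
- Low distress: "PTS < 24 months or ZBI-12 < 10 or ZBI-1" at one of its three lowest answers. Contact and reassessment are quarterly.

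**Intervention design.** Low strain needs a low burden (ZBI-12 below 10, or ZBI-1 at one of its three lowest answers) "and a stable home care arrangement (Perseverance Time Scale > 24 months) are considered as low strain". The next sentence covers the other two levels: "Dyads with a moderate to high caregiver burden (ZBI-12 10–19 or ZBI-1" at its second-highest answer for moderate, and ZBI-12 of 20 or more or the top ZBI-1 answer for high. On stability it has "a moderate to low care arrangement stability (Perseverance Time Scale < 24 months and > 6 months, and < 6 months" for moderate and high in turn. These lead to monthly and weekly contact respectively.

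The Mobile health app section says that the app's repeated short assessments sort dyads into three intensity levels, and that the level also sets how often the app reassesses. The Primary outcome section lists six PTS answers, of which the longest is two years or more. Under Trial status, recruitment began in January 2026 and the current protocol is version 2.0 of 20.02.2026.

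**The concern.** A rule that assigns contact frequency should give each set of answers one level. Table 1 does not: one of its conditions is empty, others are nested inside each other, and several differ from the text that describes the same rule. A caregiver who expects to manage for less than one week meets the PTS condition of both the high row and the low row.

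The Introduction suggests that earlier dyadic interventions gave mixed results partly because of their duration and intensity, and because rising needs were not met promptly enough. The intensity rule is therefore a central part of what is being tested. Someone who later compares delivered with scheduled contact, or repeats the intervention, needs a single statement of the schedule. Dyads may already be stratified, since recruitment is under way.

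**Working it through.** The plan gives no figure to reproduce here. The check sets the two statements side by side and then applies each one literally.

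**1. Criteria side by side**

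| Element | Table 1 | Intervention design text |
|---|---|---|
| High, PTS | < 6 months | < 6 months |
| Moderate, PTS | < 6 and > 24 months (empty) | > 6 and < 24 months |
| Low, PTS | < 24 months | > 24 months |
| High, ZBI-12 | ≥ 20 | ≥ 20 |
| Moderate, ZBI-12 | < 20 | 10–19 |
| Low, ZBI-12 | < 10 | < 10 |
| Low, link between burden and PTS | or | and |

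The table's low PTS range contains the whole high range and excludes the answer of two years or more. Its moderate ZBI-12 range contains the low range.

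**2. PTS alone.** The text's > 24 months is read as the answer of two years or more.

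| PTS answer | Table 1 | Text |
|---|---|---|
| The three answers below 6 months | high and low | high |
| Less than 1 year; less than 2 years | low | moderate |
| 2 years or more | no level | low |

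All six answers are classified differently.

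**3. PTS crossed with ZBI-12, ZBI-1 ignored.** H, M and L are the levels met.

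Table 1: H if PTS < 6 or ZBI-12 ≥ 20; M if ZBI-12 < 20, since its PTS part is empty; L if PTS < 24 or ZBI-12 < 10.

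Text: H if PTS < 6 or ZBI-12 ≥ 20; M if PTS 6–24 or ZBI-12 10–19; L if PTS ≥ 24 and ZBI-12 < 10.

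| PTS (months) | ZBI-12 | Table 1 | Text |
|---|---|---|---|
| < 6 | < 10 | H, M, L | H |
| < 6 | 10–19 | H, M, L | H, M |
| < 6 | ≥ 20 | H, L | H |
| 6–24 | < 10 | M, L | M |
| 6–24 | 10–19 | M, L | M |
| 6–24 | ≥ 20 | H, L | H, M |
| ≥ 24 | < 10 | M, L | L |
| ≥ 24 | 10–19 | M | M |
| ≥ 24 | ≥ 20 | H | H |

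- Table 1: two combinations meet three levels, five meet two and two meet one. So 2 + 5 = 7 of 9 are ambiguous. Four meet both H (weekly) and L (quarterly): the three with PTS < 6, and PTS 6–24 with ZBI-12 ≥ 20.
- Text: 7 of 9 meet exactly one level. The other two are H/M overlaps, weekly against monthly.

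**4. Adding ZBI-1.** In the text, PTS above 24 months with ZBI-12 below 10 meets low strain whatever the ZBI-1 answer, because ZBI-12 and ZBI-1 are alternatives. With ZBI-1 at *extremely* the same dyad also meets high. So the text, too, can give weekly and quarterly contact for one set of answers.

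A full count uses 6 PTS answers × 49 ZBI-12 scores × 5 ZBI-1 answers = 1470 profiles. It assumes a ZBI-12 range of 0–48, which the article does not state.
- Table 1: 29 (high only) + 10 (moderate only) = 39 of 1470 profiles meet exactly one level, or 2.7%. None is low only.
- Text: 497 + 170 + 30 = 697 of 1470 meet exactly one level, or 47.4%.

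**5. Effect of a precedence rule.** Neither statement gives one.
- Highest level first: Table 1 gives 1230 high, 240 moderate and 0 low; the text gives 1230, 210 and 30. The two differ in 30 profiles (PTS of two years or more, ten ZBI-12 scores below 10, three lowest ZBI-1 answers: 1 × 10 × 3).
- Lowest level first: Table 1 puts 495 + 667 + 230 = 1392 of 1470 profiles in low.

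The profiles are unweighted. They show how far the rule is undetermined and are not expected shares of caregivers.

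**The case against.** The best defence is that Table 1 is a misprinted summary and the text shows what was meant. The text's PTS and ZBI-12 bands are coherent, and on the 3 × 3 grid they leave only two overlaps, both between adjacent levels. The article also gives a direction: Intervention design says that intensity rises with higher burden or lower stability, and the Mobile health app section says much the same. Read as highest level first, table and text differ in only 30 of 1470 profiles.

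Much of this stands. It limits the point but does not remove it. Nothing says that the text overrides the table. The stated direction is not a formal precedence rule. The 30 profiles are also the whole quarterly level under that reading, so Table 1 would leave that level empty. A reading error from the PDF is an unlikely explanation: several characters would have to be wrong, and the conflict between *or* and *and* is not a symbol error.

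A reader might infer more: that no usable rule exists, that sites or app builds are delivering different interventions, or that the trial could not say what it tested. The documents do not support this. The text offers a largely workable alternative. Stratification runs through the app, for which the oversight section makes one institution responsible, and no site-level scoring or multiple builds are mentioned. Contact frequency is also only part of an intervention with four key components.

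An article may leave operational detail to the full protocol. The point here is a contradiction between two printed rules, not an omission.

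**Conclusion.** The point holds as an internal contradiction in stated decision thresholds. Table 1 contains a PTS condition that can never be met, overlapping ranges, and three departures from the Intervention design text: the direction of the low PTS cut-off, the lower bound of moderate ZBI-12, and *or* in place of *and*. As printed, 7 of 9 PTS by ZBI-12 combinations meet more than one level of Table 1, and four of them meet both the weekly and the quarterly row.

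These counts rest on literal reading, on ignoring ZBI-1, and on reading more than 24 months as the answer of two years or more. The contradictions themselves do not depend on the assumed ZBI-12 range.

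The reach is limited. The levels govern delivery in the intervention arm only. Sample size, alpha and the primary ordinal model are unaffected. The app may already hold a coherent algorithm, but the article cannot show that.

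**What to change.** Reconcile Table 1 and the Intervention design text into one rule, used in both places:
- levels that are mutually exclusive and exhaustive, written in the six actual PTS answers;
- explicit *and*/*or* logic between PTS, ZBI-12 and ZBI-1;
- a stated precedence for answers that point to different levels.

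Then confirm that the app's algorithm matches the reconciled rule. Recruitment began in January 2026, so this check should not wait. Which cut-offs and which precedence apply is for the sponsor's clinical team to decide.

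The cost is a correction to one table and one paragraph, plus a check of the app configuration.

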**Fig. 1 Fig1:**
[figure not shown]
Schematic overview of trial design

## Methods: participants, interventions, and outcomes

### Study setting {9}

The study is set within the patients’ homes and the context of specialized outpatient healthcare provision (memory clinics) in Germany.

### Eligibility criteria {10}

Eligible participants are dyads consisting of a PlwD and an informal caregiver. The PlwD must have a formal diagnosis of dementia and reside in his/her own home. The informal caregiver must be the primary caregiver of the PlwD with access to a mobile device with online capabilities. The dyad must reside within the catchment regions of the participating memory clinics to facilitate home visits.

### Who will take informed consent? {26a}

Participating dyads will receive all relevant information on the study’s objectives, procedures and risks before registration. Both the PlwD and the informal caregiver need to give written informed consent prior to the study. The written study information and the consent form are adapted for the two participating groups; for example, for the PlwD, the forms are reformulated in a simplified format. If the PlwD is unable to consent, their legal representative will be asked to provide written informed consent on their behalf. Physicians in the recruiting memory clinics will be responsible for ensuring the PlwD’s ability to provide informed consent. The original declarations will be kept safely at the respective study center. Participants (and caregivers) will receive a copy. Study participants can withdraw their consent at any time without negative consequences for them. In case of revocation, all personal data of the participant will be anonymized or deleted, if necessary (at DZNE).

### Additional consent provisions for collection and use of participant data and biological specimens {26b}

Participants may choose to consent or decline to provide a hair sample for cortisol-level analysis.

## Interventions

### Explanation for the choice of comparators {6b}

Dyads in the control group will receive care as usual, reflecting the current standard of care in German memory clinics and subsequent outpatient treatment and care.

### Intervention description {11a}

#### Intervention design

The intervention consists of a structured, individualized, dyadic, collaborative approach, identifying and addressing the needs of both the PlwD and the informal caregiver. Family Care Specialists (qualified nurses) identify the care and support needs of the dyad using a tablet-based intervention management system (IMS).

In general, the intervention consists of four key components:i.Initial needs assessment at the memory clinic, followed by a home visit with a comprehensive initial resource and need assessment of the dyads in their current home-living situation. In these assessments, comprehensive information regarding the medical, psychological, pharmaceutical, social and nursing situation is collected to identify the individual resources and unmet needs of both the caregiver and the PlwD. The information collected informs the subsequent selection of intervention tasks, which are then tailored by the Family Care Specialist to the dyad’s context and preferences.ii.Generation of an individual intervention task list based on the identified unmet medical, psychosocial, and care-related needs. While the system does not explicitly assess personal life history, the Family Care Specialist evaluates the suitability of the suggested tasks for the dyad and adapts them as necessary to match the dyad’s capabilities, preferences, and context.iii.Collaborative completion of the task list by the Family Care Specialist in close cooperation with the treating general practitioner of the caregiver and the PlwD and other healthcare and social services providers involved in the care for either the caregiver, or the PlwD, or both during the 12-month intervention period. Tasks are reviewed and adjusted collaboratively with the dyad to ensure they are feasible and appropriate. The Family Care Specialist may also add tasks not predefined in the IMS if these better align with the dyad’s needs and preferences.iv.Access to a mobile health app for caregivers for digital support, caregiver burden monitoring, and connection to the Care Specialist and the memory clinic at any time, enabling timely response as well as identification of emerging unmet needs and additional intervention tasks.

The content, the frequency and intensity of the intervention tasks are adjusted according to the caregiver’s burden and the stability of the home care situation, meaning that the higher the burden or the lower the home care stability, the more frequent and intense the intervention will be. Dyads with a low caregiver burden (ZBI-12 < 10 or ZBI-1 “not at all/little/moderately”) and a stable home care arrangement (Perseverance Time Scale > 24 months) are considered as low strain and will be contacted by the Family Care Specialist on a quarterly basis to check on their needs. Dyads with a moderate to high caregiver burden (ZBI-12 10–19 or ZBI-1 “quite a bit”, and ZBI-12 ≥ 20 or ZBI-1 “extremely”) or a moderate to low care arrangement stability (Perseverance Time Scale < 24 months and > 6 months, and < 6 months) are considered as medium to high strain resulting in a monthly or weekly contact frequency, respectively.

Besides these regular contacts (executed via a visit at the home of the PlwD or the caregiver or a phone call or a video call via the mobile health app) the caregivers can reach out to the Family Care Specialists anytime to seek assistance or advice. 

